**Materials and methods:**

In total, 120 bariatric patients will be randomized between RYGB and OAGB in two academic centers. All patients will be followed up for 10 years with analysis and measurements of weight, comorbidities, blood tests, body composition and questionnaires. Extensive metabolic analyses (mixed meal tests, energy expenditure, biopsies of muscle and subcutaneous fat, urine, saliva and fecal samples) will be carried out in the Obesity Research Unit, University of Helsinki, for all patients treated at the Helsinki University Hospital (80 patients) at baseline, 6 months and 12 months. Bile reflux will be studied for the OAGB group at the Helsinki University Hospital at 6 months with gastroscopy and scintigraphy.

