## Introduction

Surgery is the most effective treatment for morbid obesity, and gastric bypass has been considered a gold standard [1, 2]. Currently there are several viable options for performing a gastric bypass. Roux-en-Y gastric bypass (RYGB) has been modified from the bypass method published by Mason and Ito in the 1960s [3]. The hallmarks of RYGB are a small gastric pouch anastomosed to an alimentary limb and a separate biliopancreatic (BP) limb [4]. In 2001 Rutledge published a technique called mini-gastric bypass (MGB; later termed one-anastomosis gastric bypass (OAGB) or single-anastomosis gastric bypass (SAGB)) with a longer tubular-shaped pouch and a longer BP limb anastomosed directly into the distal end of the gastric pouch [5]. Since then, and according to the International Federation for the Surgery of Obesity and Metabolic Disorders 2018 statement on MGB/OAGB/SAGB procedures, a preferred term for all bypasses with a long gastric pouch and a long BP limb should be OAGB [6].

RYGB and OAGB have both shown excellent weight-loss results in many cohort series and prospective trials [7–9]. However, to our knowledge only two prospective randomized controlled trials comparing RYGB and OAGB have been published [10, 11]. It has been stated that OAGB would be at least as effective, faster to perform and less prone to complications such as internal herniations compared to RYGB [12]. On the other hand, it has been suggested that OAGB can cause bile reflux, a potential risk for premalignant Barrett’s metaplasia of the esophagus. OAGB has been proposed to have a more favorable effect on type 2 diabetes mellitus (T2DM) but might be more prone to nutritional deficiencies [6, 11]. The BP limb is usually longer in OAGB compared to RYGB, which most likely affects T2DM remission, but limb lengths have not been standardized in either procedure. Overall, there are a lot of unanswered questions when comparing RYGB and OAGB. A recent meta-analysis on this subject concluded that a larger sample size and multicenter randomized controlled trials are needed to compare the effectiveness and safety between these procedures [13].

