## Materials and methods

### Aims of the study

The primary outcome is weight loss 2 years after the operation. Weight loss is measured as percentage excess weight loss (%EWL) and percentage total weight loss (%TWL). %EWL is calculated as a percentage of lost excess weight since the preoperative visit compared to an ideal weight with a body mass index (BMI) of 25 kg/m^2^. Weight loss will also be analyzed as a grouping variable according to different categories of weight loss to compare responders and nonresponders to bariatric surgery. For EWL% we use the categories 0–24.99%, 25–49.99%, 50–74.99% and ≥75%, and for TWL% we use the categories <10%, 10–19.99%, 20–29.99%, 30–39.99%, ≥40% to determine participants with different amounts of weight loss achieved.

The secondary outcomes to be measured at the time points of 6 months, 12 months, 24 months, 5 years and 10 years are as follows:
Weight loss (%EWL, %TWL)Complications (any complication requiring any intervention or a prolonged hospital stay or additional outpatient visits)Perioperative factors (operation time, hospital stay, nausea, ability to take fluids and mobilization)Remission of comorbidities (including, for example, T2DM, hypertension, nonalcoholic fatty liver disease); remission is defined as normalization of measured values without medicationChanges in nutritional, metabolic and safety laboratory parameters (e.g., hemoglobin, vitamins, albumin, electrolytes, liver enzymes, lipids)Glucose tolerance and insulin response during an oral glucose tolerance test (OGTT) or meal testContinuous glucose monitoring (CGM)Changes in body composition (whole body fat with dual-energy x-ray absorptiometry (DEXA) and bioelectrical impedance (BIA), lean mass (DEXA and BIA), bone mineral mass and density (DEXA), subcutaneous fat (magnetic resonance imaging (MRI)), intra-abdominal fat (MRI), liver fat (magnetic resonance spectroscopy (MRS))Bile reflux at 6 months (for the OAGB group at Helsinki University Hospital (HUH))Tendency for urolithiasisChanges in cortisol and other hormone metabolismChanges in blood and tissue (adipose tissue, muscle) transcriptomics, proteomics, metabolomicsChanges in tissue (adipose tissue, muscle) mitochondrial activitiesChanges in gut and saliva microbiota and bile acid metabolismChanges in quality of life and lifestyle and gastrointestinal symptoms

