Drop-out and lost-to-follow-up patients will be included in the analyses with measurements and values that have been obtained prior to drop-out. A 10% drop-out rate has been included in the power calculation regarding the primary outcome. Patients are regarded as part of their original treatment group according to randomization on an intention-to-treat basis.

An interim analysis regarding safety and trial progression has been performed after half of the patients have been randomized and undergone surgery.

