### Statistical analyses

Normally distributed variables will be expressed as the mean and SD, and non-normally distributed variables will be expressed as the median and interquartile range; categorical variables will be expressed as the number and percentage.

To test the group differences (OAGB vs RYGB) in the primary and secondary endpoints, we will use the Student’s *t* test for continuous normally distributed variables, the Mann–Whitney *U* test for continuous non-normally distributed data, and the chi-squared test or Fisher’s exact test for categorical variables. Additionally, we will conduct multivariable analysis with generalized mixed linear regression or logistic regression models with adjustment for possible confounding factors. The statistical analyses will be conducted on an intention-to-treat basis. A *P* value < 0.05 will be considered statistically significant.

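### Complications read out to 10 years are compared as simple proportions with drop-outs kept in on pre-drop-out data, so absolute late risks are likely to read low and the arm difference can be distorted

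*Protocol article*

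**What the plan says.** Under Aims of the study, the secondary outcomes are introduced with "The secondary outcomes to be measured at the time points of 6 months, 12 months, 24 months, 5 years and 10 years are as follows". Complications are on that list, defined as "any complication requiring any intervention or a prolonged hospital stay or additional outpatient visits". The Abstract gives the horizon: "All patients will be followed up for 10 years".

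Statistical analyses sets the tests for primary and secondary endpoints by type of variable. Categorical variables get "the chi-squared test or Fisher’s exact test for categorical variables". Mixed linear or logistic regression is added, and everything is by intention to treat. No method that uses time at risk is named.

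The drop-out rule is also in Aims of the study: "Drop-out and lost-to-follow-up patients will be included in the analyses with measurements and values that have been obtained prior to drop-out". The only loss figure belongs to the 2-year endpoint: "A 10% drop-out rate has been included in the power calculation regarding the primary outcome". Nothing is said about expected loss at 5 or 10 years.

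**The concern.** A complication accrues with time at risk. A proportion test at 10 years needs a yes or no for every patient in the denominator. Take a patient who leaves at month 12 without a complication. The drop-out rule keeps that patient in, and the only recorded information is that nothing had happened by month 12. The 10-year count can then hold the patient only as a non-event, although nobody observed years 1 to 10. For weight, a pre-drop-out value is at least an observation of weight; for an accruing harm, unobserved time becomes absence of harm. The logistic model inherits the same outcome and does not repair this.

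Safety is one of the comparisons the Conclusion section promises. The Introduction reports a claim that OAGB is "less prone to complications such as internal herniations compared to RYGB". The trial is open-label with unblinded outcome analysis (Study sites and randomization), so loss that differs between arms is plausible. If late risks read low, or the arm difference moves because follow-up differs, the long-term safety comparison would mislead.

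**Working it through.** **The plan's own figures.** No figure is stated for complications. The primary sample size (difference of 10 in %EWL, SD 17, 50 per group, 80% power) reproduces: simulated Mann-Whitney power at 50 per group is 80.8%, and 50 × 1.1 = 55. Nothing below touches it.

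**Inputs.** From the documents: 60 per arm, 10-year follow-up, drop-outs kept in. Assumed, because the documents are silent: 10-year complication risk F per arm, loss d by year 10, constant hazards, loss independent of complications.

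**Formulae.** Event hazard h = −ln(1 − F)/10; loss hazard c = −ln(1 − d)/10. True 10-year risk = F. Risk as counted when lost patients stay in the denominator = h/(h + c) × [1 − exp(−10(h + c))], and the bracket equals 1 − (1 − F)(1 − d).

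*Worked case, F = 20%, d = 30%.* h = 0.02231, c = 0.03567, h/(h + c) = 0.385, bracket = 1 − 0.80 × 0.70 = 0.44, counted risk = 0.385 × 0.44 = 16.9%.

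**Equal loss, true risks 20% vs 5% (difference 15.0 points, ratio 4.00)**

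| Loss by year 10 | Counted risks | Difference | Relative fall | Risk ratio |
|---|---|---|---|---|
| 10% | 19.0% vs 4.75% | 14.3 | 5% | 4.01 |
| 30% | 16.9% vs 4.2% | 12.7 | 15% | 4.02 |
| 50% | 14.6% vs 3.6% | 11.0 | 27% | 4.04 |

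For 30% vs 15% and 40% vs 20%, the falls at 50% loss are 26% and 25%. If all events fall in years 5 to 10, the 15.0 points become 13.9, 11.5 and 9.0 at 10%, 30% and 50% loss: falls of 8%, 23% and 40%.

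**Extending the plan's 10% per 2 years.** This is an extrapolation: 1 − 0.9^2.5 = 23% lost at 5 years and 1 − 0.9^5 = 41% at 10. With assumed risks of 12% vs 4%, the arms read 9.4% vs 3.1%, so 8.0 points become 6.3 (22% lost), while the ratio goes from 3.00 to 3.01. At 2 years the fall is only about 5%.

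**Unequal loss.** True 30% vs 15% (15.0 points, ratio 2.00):
- Higher-risk arm loses 10%, the other 40%: 28.6% vs 11.8%, difference 16.7, ratio 28.56/11.83 = 2.41.
- Reversed: 23.9% vs 14.3%, difference 9.6, ratio 23.85/14.26 = 1.67.

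With equal true risk of 15% and losses of 20% vs 40%, the arms read 13.5% vs 11.8%. The risk ratio is therefore stable only when loss is similar.

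**What a time-to-event analysis recovers.** In 3,000 simulated trials (20% vs 5%, 60 per arm, equal loss), the Kaplan-Meier risk difference averages 15.1, 14.9 and 14.7 points at 10%, 30% and 50% loss. Power at 30% loss is 65% for chi-squared, 65% for log-rank and 52% for Fisher.

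**The case against.** Four points deserve weight.

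*The scoring rule is inferred.* The article never says that a lost patient counts as complication-free. Outcomes are read at separate time points, so the patient could contribute at 6 and 12 months and have no 10-year value. Analysing only those followed to 10 years is unbiased if loss is independent of events. It stands that this is an inference. But that alternative sits badly with the drop-out rule, because it discards complications recorded before a patient left. With F = 20% and d = 30%, 16.9% of an arm has a recorded event, but only 0.20 × 0.70 = 14.0% remains among those still followed; the gap is about 1.8 patients in 60. Keeping those events while removing only the event-free losses errs the other way: 0.1693/(0.1693 + 0.56) = 23.2% and 0.0421/(0.0421 + 0.665) = 6.0%, a difference of 17.3 points against 15.0. No simple proportion keeps every recorded event and avoids the problem.

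*This is analysis-plan detail.* Denominators and censoring often belong there. Here, however, the article itself fixes both the family of tests and the drop-out rule, and the two do not suit an accruing event.

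*The size is assumed and small beside sampling error.* In the 12% vs 4% example the shift is 1.7 points, about one patient in 60, against a standard error of √(0.12 × 0.88/60 + 0.04 × 0.96/60) = 4.9 points. This is fair, and it keeps the point at the level of a secondary safety outcome. The article also concedes limited power for some secondary outcomes.

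*Internal herniation is background.* It appears in the Introduction as something others have claimed and is not a listed outcome. That also stands.

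**Conclusion.** The point holds as a mismatch between a stated test, a stated drop-out rule and an outcome that accrues over 10 years. On the natural reading, absolute complication risks at 5 and 10 years read low whenever there is loss. With similar loss in both arms the risk difference falls by about 5% (relative) at 10% loss by year 10, 15% at 30% and 25% or more at 50%, and by more if events come late. All of this rests on assumed risks, assumed late loss and independence of the two; at 2 years, the only horizon with a stated drop-out allowance, the effect is about 5%.

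A reader might infer that the plan will certainly under-report late harms and shrink the difference between procedures. The documents do not support that. They do not state the event-free scoring, they give no late loss or complication rates, the risk ratio is almost unchanged under similar loss, and unequal loss can inflate the difference as well as reduce it. Nor does a time-to-event test buy power. The primary weight-loss analysis and its sample size are unaffected. The change should be made, but the trial's main conclusion does not depend on it.

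**What to change.** In Statistical analyses, take post-discharge complications out of the chi-squared/Fisher rule. Analyse time from operation to first complication, censored at last contact, with death as a competing event. Report cumulative incidence per arm and the risk difference with 95% CI at 6, 12 and 24 months, 5 and 10 years, with a log-rank or Gray test if a p value is wanted. Keep Fisher's exact test for in-hospital events, where follow-up should be complete.

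In Aims of the study, add to the drop-out rule that for event outcomes patients are censored at last contact and are not carried forward as event-free. Also report follow-up time and loss by arm, because censoring is sound only if loss is unrelated to complications. A separate analysis of internal herniation or reoperation is optional.

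The cost is a few sentences, a little more analysis, and dates for each complication and each last contact. The article does not say that these dates are recorded, so this should be confirmed. Late confidence intervals will be wider because they reflect the number actually under observation.

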### Sample size

This study is designed as a superiority trial based on previous cohort series. According to power calculations finding a difference of 10 in %EWL with the assumptions of mean %EWL = 60 (standard deviation (SD) = 17) in the RYGB group, with alpha = 0.05, 50 patients in each group would be sufficient to reach the power of 80%. If a drop-out of 10% is taken into account, this would mean 55 patients per group. Power calculations were performed by simulation using the Mann-Whitney-Wilcoxon test (PASS v13.0, NCSS Inc., Kaysville, Utah, USA). Since there was a lack of published data on comparisons between these two operations at the time of designing the study, we decided to recruit 60 patients for both treatment groups in order to have sufficient statistical power regarding the primary end point (10% difference in %EWL at 2 years between the groups).

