### Study sites and randomization

The trial is being carried out in two academic centers: HUH in collaboration with the University of Helsinki, and Oulu University Hospital (OUH). Both bariatric centers (HUH and OUH) are university hospitals that are tertiary referral bariatric centers with a catchment area of around one million people in Finland. Metabolic studies for patients in HUH are conducted by the Research Program for Clinical and Molecular Metabolism, University of Helsinki.

The trial is carried out according to the Consolidated Standards of Reporting Trials (CONSORT) statement. The trial schedule is shown in Fig. 1. Surgeons performing the intervention recruit eligible patients at a preoperative visit (study baseline) and randomize them according to protocol. This is an open-label study and the patients and surgeons are informed of the randomization outcome. Outcome analyses are also performed without blinding. Randomization is carried out as follows: 120 sheets of paper stating either “Single Anastomosis Gastric Bypass” or “Roux-en-Y Gastric Bypass” are divided into groups of four and six containing equal numbers of both outcomes and then sealed into opaque envelopes. These groups of opaque envelopes are distributed to both centers (80 envelopes for HUH and 40 envelopes for OUH) and then divided into two batches (for patients with diabetes and those without). The goal of this allocation sequence is to have equal numbers of patients in both groups at both centers and also an equal number of patients with diabetes in both groups at both centers.

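### The primary endpoint is tested without adjustment, by a t or Mann-Whitney test depending on its distribution, although allocation is stratified and %EWL depends on baseline BMI: valid, but less precise than one prespecified adjusted model

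*Protocol article*

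**What the plan says.** All references are to the protocol article.

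- **Endpoint (Aims of the study).** "The primary outcome is weight loss 2 years after the operation", expressed as %EWL and %TWL. %EWL is the "lost excess weight since the preoperative visit compared to an ideal weight" at a BMI of 25.
- **Planning (Sample size).** The target is "finding a difference of 10 in %EWL", assuming "mean %EWL = 60 (standard deviation (SD) = 17) in the RYGB group", with alpha 0.05, 80% power and 50 patients per group. This becomes 55 with 10% drop-out, and 60 per group are to be recruited. "Power calculations were performed by simulation using the Mann-Whitney-Wilcoxon test".
- **Allocation (Study sites and randomization).** Envelopes in blocks of four and six go to the two centres (80 and 40) and are then "divided into two batches (for patients with diabetes and those without". The stated aim is balance on both factors. The same section adds: "Outcome analyses are also performed without blinding".
- **Analysis (Statistical analyses).** One rule covers primary and secondary endpoints: t test for normally distributed continuous variables, Mann-Whitney for the others. Then: "Additionally, we will conduct multivariable analysis with generalized mixed linear regression or logistic regression models with adjustment for possible confounding factors". Centre, diabetes status and baseline BMI are not named there.

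**The concern.** Three features of the plan do not fit together.

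1. The trial balances the arms on centre and diabetes status by design, but the test given first for the primary endpoint does not use either factor. When such factors predict outcome, stratified allocation removes their contribution from the between-arm difference, while an unadjusted test still counts it in the standard error. The standard error is then too large and the test slightly conservative.
2. %EWL is a function of baseline BMI by construction. Patients with the same proportional weight loss get different %EWL values if they start at different BMIs. That spread is noise in an unadjusted comparison and can be removed with a value already measured at baseline.
3. The planning target is a difference in %EWL from a stated mean, the sizing test is a rank test, and the analysis may be either. A t test addresses a difference in means and a Mann-Whitney test compares distributions by rank. The text does not say which of these, or the adjusted model, decides the trial.

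At stake are some power and a clear statement of the primary result, not the validity of the trial.

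**Working it through.** **1. Reproducing the sample size.** Inputs from Sample size: difference 10, SD 17 (taken as equal in both arms), alpha 0.05 (taken as two-sided), power 80%.

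- Normal approximation: n = 2 × [17 × (1.960 + 0.842)/10]² = 45.4, so 46 per group. The t-test solution is 46.3.
- Mann-Whitney, dividing by the relative efficiency 3/π: 47.5 to 48.5 per group.
- Mann-Whitney simulated on normal data (20,000 runs): power 79.0% at 48, 80.6% at 49 and 81.5% at 50 per group.

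The stated 50 per group is reproduced.

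**2. Unadjusted power at the expected number of completers.** 60 × 0.90 = 54 per arm. SE = 17 × √(2/54) = 3.27 points. The t test has 85.7% power; the simulated Mann-Whitney test has 83.7%.

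**3. How %EWL depends on BMI.** With ideal weight at BMI 25, %EWL = %TWL × BMI/(BMI − 25). The interim RYGB BMI is 44.0 with SD 5.9 (Interim results).

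- At BMI 44.0 the factor is 44/19 = 2.316, so 60 %EWL corresponds to 60/2.316 = 25.9 %TWL.
- At BMI 38.1 (one SD below) the factor is 2.908, and the same %TWL gives 75.4 %EWL.
- At BMI 49.9 (one SD above) the factor is 2.004, and the same %TWL gives 51.9 %EWL.

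The spread is about 23 points, against a target difference of 10. This does not carry over to %TWL, which has no such denominator.

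**4. What correlation that implies.** The documents do not give one, so this is an assumption. I simulated BMI with mean 44.5 and SD 5.7, truncated at the inclusion limit of 35, and %TWL with mean 26 and residual SD 6.

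| %TWL change per BMI unit | Correlation of BMI with %EWL |
|---|---|
| 0 (independent) | −0.53 |
| +0.4 points | about −0.28 |
| +0.6 points | about −0.12 |

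Under independence the simulated %EWL SD is about 17, matching the planning value. A range of 0 to 0.5 in absolute size is reasonable to show.

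**5. Power after adjustment.** Residual SD = 17 × √(1 − r²), 54 per arm, difference 10, two-sided 0.05, t test:

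| r | Residual SD | SE of difference | Power | Equivalent sample-size factor 1/(1 − r²) |
|---|---|---|---|---|
| 0 | 17.0 | 3.27 | 85.7% | 1.00 |
| 0.3 | 16.2 | 3.12 | 88.8% | 1.10 |
| 0.4 | 15.6 | 3.00 | 91.1% | 1.19 |
| 0.5 | 14.7 | 2.83 | 93.8% | 1.33 |

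**6. Error rates with balanced strata.** Simulation of 6,000 trials per scenario, 54 per arm, unadjusted t test against a linear model with four strata and BMI. The R² values are assumed.

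| R² strata / R² BMI | Null rejection, unadjusted | Null rejection, adjusted | Power, unadjusted | Power, adjusted |
|---|---|---|---|---|
| 0 / 0 | 4.8% | 4.8% | 85.6% | 85.4% |
| 0.05 / 0.05 | 4.5% | 4.7% | 86.3% | 89.1% |
| 0.10 / 0.10 | 4.0% | 5.0% | 87.2% | 92.4% |
| 0.10 / 0.20 | 3.9% | 5.1% | 86.8% | 95.3% |

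The last row has a total R² of 0.30, beyond the r = 0.5 (R² = 0.25) used in step 5.

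**7. Choosing between the two tests.** The article gives no criterion, so a Shapiro-Wilk check was assumed. Type I error was 4.8% with normal data and 5.2% with skewed data. At a true difference of 10, the t and Mann-Whitney tests gave opposite verdicts in about 4% (normal) to 7% (skewed) of simulated trials.

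**The case against.** The best defence is that nothing here is invalid. An unadjusted comparison is legitimate after stratified randomisation, the sample size reproduces, and 54 completers per arm already give about 86% power. Choosing the test by a normality check did not inflate type I error in simulation. An adjusted analysis is also planned, and its wording excludes neither the strata nor BMI. All of this stands, and it limits the point to precision and clarity.

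Several stronger readings are tempting, and the documents do not support them.

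- **Inflated false positives or an underpowered trial.** A reader might infer either from the ignored strata. Step 6 shows the opposite direction for type I error, and step 2 shows the power target is met at the planning SD.
- **Centre as an established source of outcome variance.** The centres differ in stapler length, defect closure and the 3-month contact. No weight loss by centre is reported, and nothing links these differences to 2-year weight. Nor is a diabetes effect on %EWL given.
- **Unnamed covariates and unblinded analysis as proof that results could be selected.** The covariate list, the normality criterion and any coding of arms are details that an analysis plan not shown here may hold. That the test is picked after inspecting the data is the natural reading, but no check or timing is described.

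It can also be said that demoting the Mann-Whitney test departs from the test used for sizing. That is true. But the stated target is a 10-point difference from a stated mean, which a linear model estimates directly.

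**Conclusion.** The point holds as an efficiency and clarity improvement. The article itself ranks an unadjusted, distribution-dependent test ahead of adjustment for the primary endpoint, so this is a stated choice and not a detail left out.

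The gain is 0 to about 8 percentage points of power (about 86% to at most 94%) for a covariate correlation of 0 to 0.5, at SD 17, 54 per arm and a 10-point difference. The upper end needs %TWL to be unrelated to baseline BMI; if %TWL rises with BMI the gain shrinks, and at zero correlation it vanishes. The BMI denominator argument concerns %EWL only. The slight conservatism of the unadjusted test likewise depends on the strata being prognostic, which is plausible but not shown.

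Confidence is high on what the plan states and on the direction of the effect, and moderate on its size.

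**What to change.** Name one primary analysis: a linear model of 24-month %EWL on arm, centre, diabetes stratum and baseline BMI, reporting the adjusted mean difference (OAGB minus RYGB) with its 95% confidence interval, whatever the distribution looks like. Keep the unadjusted t and Mann-Whitney tests as sensitivity analyses. Record this in the protocol or analysis plan before the 24-month data are opened.

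The cost is wording. Centre and diabetes status are known at randomisation and BMI is measured at baseline, so no patients, visits or measurements are added.
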